#### Sampling.

The sampling methodology for both surveys is designed to be representative of the PHC health facilities in Tajikistan at the national and oblast (region) levels. Since the role of private sector in providing PHC services is minimal in Tajikistan, the sample frame consists of all public PHC health facilities in the country comprising of- City and District Health Centers (family medicine departments), Rural Health Centers, and Health Houses. The sample was stratified across all oblasts. To obtain quality results from the comparison of the rapid phone-based HFA and the comprehensive in-person HFA, each survey will be conducted in the identical sample of 500 facilities described in Table 2.

**Table 2 pone.0309570.t002:** Sample for the rapid-phone based and comprehensive in-person HFAs.

		# Facilities	# Selected
Oblast	Dushanbe	15	15
	Sughd	616	151
	Khaktlon	1,123	150
	Gorno-Badakhshan Autonomous Region	227	84
	Districts of Republican Subordination	713	100
Type	City Health Center	41	41
	District Health Center	53	53
	Rural Health Center	895	214
	Health House	1,705	192
**TOTAL**		**2,694**	**500**
		

The enumerators will obtain verbal consent for the rapid phone-based HFA and written consent for the comprehensive in-person HFA from the respondents before starting the survey. If a respondent declines to participate, the reason for their refusal will be documented, and the facility will be replaced by a facility from the same strata whenever available. In the event of a non-response, health facilities will be replaced from a “replacement list” curated from the sample frame for each survey, following the same protocol of random sampling selection. Furthermore, in the event of a non-response, replacements for the two surveys will be done independently. This means that if a facility does not participate in the rapid phone-based HFA and needs to be replaced with another health facility, it will not be simultaneously replaced in the comprehensive in-person HFA, and vice-versa, unless the non-participation is due to the closure of the facility. As a result, the final samples may differ slightly due to varying response rates.

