#### Objective three: non-response rate.

Although both surveys will initially include the same sample of 500 facilities, we expect that the final samples for each HFA will differ in the end due to varying non-response rates. A simple-t test will be used to assess whether there is a significant difference in the response rates between the rapid phone-based HFA and the comprehensive in-person HFA. Balance tests will also be used to assess whether the characteristics of the final sample of included facilities (the original sample plus any replacements) for the comprehensive in-person HFA and the rapid phone-based HFA sample remain similar across both surveys. Finally, we will document any issues with phone service coverage and the ownership of mobile phones by facilities and respondents, as well as any reported instances of costs to the recipient.

In case a significant difference is found in response rate or sample characteristics, regression analysis will be used to assess associations with discordance in survey completion. This will be done by creating a binary variable to indicate whether the comprehensive in-person HFA was completed in a health facility, while the rapid phone-based HFA wasn’t. This binary variable will then regressed on facility characteristics and whether the rapid phone-based HFA was initiated before or after the comprehensive in-person HFA. Since the non-response rate is expected to be higher for the rapid phone-based HFA, this analysis will only be done for health facilities which complete the comprehensive in-person HFA but not the rapid phone-based HFA.

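### The Objective 3 discordance regression is restricted to facilities whose outcome is always 1, so as written it can estimate no association

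*Protocol article*

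**What the plan says.** All of the following is in the protocol article.

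- **Trigger** (Objective three: non-response rate). The follow-up, on discordant completion, is conditional; its opening sentence begins: "In case a significant difference is found in response rate or sample characteristics, regression analysis will be used to assess associations with discordance in survey".
- **Outcome** (same section). The analysis is set up as follows: "creating a binary variable to indicate whether the comprehensive in-person HFA was completed in a health facility, while the rapid phone-based HFA wasn’t".
- **Covariates** (same section). "This binary variable will then regressed on facility characteristics and whether the rapid phone-based HFA was initiated before or after the comprehensive in-person HFA".
- **Analysis set** (same section). Because phone non-response is expected to be the higher of the two, "this analysis will only be done for health facilities which complete the comprehensive in-person HFA but not the rapid phone-based HFA".
- **Replacement** (Sampling). At the outset "each survey will be conducted in the identical sample of 500 facilities". After that, "in the event of a non-response, replacements for the two surveys will be done independently", except where the facility has closed. After a refusal, "the facility will be replaced by a facility from the same strata whenever available".
- **Order** (Timing of survey administration). The order of the two surveys is randomised for each facility, half to each order.

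**The concern.** A regression of a binary outcome needs records with both values. Here the outcome definition and the analysis set are one and the same condition, so the records with value 0 are excluded by rule. The article states outcome, covariates and analysis set explicitly and they conflict, so this is not a detail left to a fuller plan. An analysis plan that followed the text would inherit the error, and one that did not would contradict the published protocol.

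What is at stake is the one planned model of which facilities complete the visit but are lost to the phone survey. It bears on how selected the paired sample is, and response and dropout form one of the three primary objectives.

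Two smaller matters belong to the same rewording. The text does not say whether replacement facilities enter this model. It also does not say what the order covariate means where the phone survey never started.

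**Working it through.** The article gives no event count, power or sample size for this regression, so there is no stated figure to reproduce.

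**1. Outcome against analysis set.** Let I = 1 if the in-person survey was completed and P = 1 if the phone survey was completed.

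- Outcome: Y = 1 if I = 1 and P = 0, otherwise Y = 0.
- Analysis set: facilities with I = 1 and P = 0.
- Hence Y = 1 for every record and its variance is 0.

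The general statement that opens Data analysis, which limits analysis to matched facilities that took part in both surveys, does not repair this. In that set I = 1 and P = 1, so Y = 0 throughout.

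**2. Numerical check.** One sample of 500 was simulated with assumed non-response of 5% in person and 15% by phone. The covariates were rural type (Rural Health Center or Health House versus City or District Health Center) and order.

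| Analysis set | n | Records with Y = 1 | Result |
|---|---|---|---|
| As written | 62 | 62 | Logistic fit did not converge, standard errors about 143 to 965; least squares gave intercept 1 and zero slopes |
| All original-sample in-person completers | 479 | 62 | Logistic model fitted, standard errors about 0.27 to 0.31 |

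Software may return output for the first row, but no coefficient is identified.

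**3. Replacements, if they entered the model.** A facility drawn only as an in-person replacement was never approached by phone, yet it has I = 1 and P = 0 and would be coded Y = 1.

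Inputs:
- 500 facilities in the original sample (Table 2).
- Table 2 selects all 41 City and all 53 District Health Centers. If replacement is within facility type (an assumption), only 214 + 192 = 406 facilities can be replaced.
- Non-response rates are not given. Assumed: in-person a = 2–10%, phone b = 5–20%, independent of each other and of facility type. No closures.

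Formulas: genuine discordant = 500 × (1 − a) × b; false discordant = 406 × a; false share = false / (genuine + false).

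| a | b | Genuine | False | False share |
|---|---|---|---|---|
| 2% | 20% | 98.0 | 8.1 | 8% |
| 2% | 5% | 24.5 | 8.1 | 25% |
| 5% | 10% | 47.5 | 20.3 | 30% |
| 5% | 5% | 23.8 | 20.3 | 46% |
| 10% | 20% | 90.0 | 40.6 | 31% |
| 10% | 10% | 45.0 | 40.6 | 47% |

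With in-person non-response no higher than phone, as the article expects, the share runs from 8% to 47%. Dropping that expectation (a = 10%, b = 5%) gives 40.6 / (22.5 + 40.6) = 64%.

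Under the same assumptions the false records fall only on rural types. With no true association, the rural versus city/district odds ratio among in-person completers would be 1 + a / ((1 − a) × b). That is 1 + 0.02 / (0.98 × 0.20) = 1.1 at the low end and 1 + 0.10 / (0.90 × 0.10) = 2.1 at the high end.

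**4. Order covariate.** A facility with Y = 1 may have had no phone interview begun. Whether the phone survey was initiated before or after the visit then depends on what counts as initiation. The randomised order exists for every originally sampled facility.

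**The case against.** The strongest reply is that this is a wording slip with recoverable intent. The restriction is justified by the expected higher phone non-response, which is a reason to model one direction of discordance and not a reason to discard the comparison group. Creating a binary variable and regressing it presupposes both values. No analyst could carry out the literal version, so the practical risk is ambiguity more than a wrong published estimate. All this is fair and limits the severity. It does not remove the fault, because the sentence names no comparison group and candidate denominators differ.

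Several stronger readings are tempting, and the article does not support them.

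- **That independent replacement will create false discordance.** The text neither includes nor excludes replacements from this regression. The phrase "the final sample of included facilities (the original sample plus any replacements") describes the sample for the balance tests only. Closures are exempt from independent replacement, and fully sampled strata have no reserve. The artefact is conditional and its size unknown.
- **That the order covariate is undefined.** Initiation can be read as the first contact attempt, and Data collection procedures requires at least five attempts where a respondent is unreachable. It is ambiguous, no more.
- **That using all 500 facilities would also fail.** The zeros would then mix three groups, but the contamination is small. At an assumed 4% in-person and 12% phone non-response, phone-only is 500 × 0.04 × 0.88 = 17.6 and neither is 500 × 0.04 × 0.12 = 2.4. That is 20 of 500 − 57.6 = 442.4 zeros, or 4.5%.
- **That nothing else shows which facilities are lost.** Balance tests, recorded refusal reasons and documentation of phone coverage address the same question, though less directly.
- **That the significance trigger is an error.** Running the model unconditionally is a preference.

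**Conclusion.** The point holds as an internal contradiction. The regression as written has an outcome with no variation and can estimate nothing, and this conclusion needs no assumed rate.

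The replacement artefact is a secondary reason for naming the original sample in the rewording. Its range of about 8% to 47% of discordant records rests on the assumed non-response rates, independence, replacement within facility type, no closures, and replacements being allowed into the model.

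Impact is moderate. The analysis is a conditional follow-up within Objective 3. A reader might infer that the response-rate comparison or the reliability and validity results are compromised, but none of them uses this regression.

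**What to change.** Replace the restricting sentence, and the order covariate in the sentence before it, with:

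> Among facilities in the original sample of 500 that completed the in-person HFA, logistic regression of phone HFA non-completion (yes/no) on facility characteristics and randomised survey order.

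This restores the comparison group (facilities that completed both surveys) and keeps the one direction of discordance that the authors wanted. It also leaves out replacements that were never approached by phone, and uses an order variable that is known for every facility in the set.

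The cost is one or two sentences of wording and no new data. The model needs only a marker for original-sample membership, completion status for each survey and the assigned order.

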### Discussion

To the best of our knowledge, this study is the first to assess the reliability and validity of a rapid phone-based HFA against a comprehensive in-person HFA. This will fill an important gap in global evidence on the reliability and validity of phone-based approaches to administer HFAs to monitor a subset of key facility-level indicators. This insight is especially critical given the rapid rise of phone-based survey approaches in LMICs following the COVID-19 pandemic [6] as an innovative method for more frequent, lower-cost, facility-level, primary data collection for select indicators.

### Strengths and limitations

Strengths of this study include careful design of the validation prior to the data collection for both studies, which enabled us to improve analytical rigor by ensuring a common sample, aligned enumerator training processes, and introduction of randomizing in the survey order, and the detailed process undertaken to adapt both surveys to the Tajikistan context. A key limitation is that the final survey instruments for the comprehensive HFA and the rapid phone-based HFA are not identical, comprising both direct and indirect mapped indicators for analytical comparison. We prioritized maintaining as much fidelity to the original phone and in-person instruments as possible, as these two instruments in their original state will be used repeatedly in Tajikistan to monitor large-scale PHC reforms. The challenges we experienced in directly aligning the two instruments is also reflective of our experience that phone and in-person instruments need to be designed and administered differently; therefore, while the lack of identical survey questions is a limitation from the perspective of statistical rigor, it also reflects a practical and operational reality of administering different types of health facility surveys.

Within the study context and the GFF’s FASTR initiative more broadly, the intent is to use low cost, high frequency phone surveys as a complement to, rather than a substitute for, periodic and more comprehensive in-person facility assessments. Most immediately, the findings of this study will be used to refine the GFF FASTR Initiative’s rapid health facility phone survey assessment prior to its scale-up in multiple countries in Sub-Saharan Africa and Asia in 2025 and beyond. Our intention is that the revised version of the survey instrument and underlying data will then be made publicly available on the GFF’s data portal (https://data.gffportal.org/), FASTR’s publicly available resource repository (https://data.gffportal.org/key-theme/FASTR/resource-repository/index.php/home), and the SDI Microdata Library (*https://microdata.worldbank.org/index.php/catalog/sdi/?page=1&ps=15&repo=sdi**).* We will also distill our operational learnings in a health facility mobile phone survey manual which will enable the broader public health research and practice community to utilize the FASTR toolset.

More broadly, findings from this study will be used to provide measurement and methodological guidance for HFAs. The findings will provide novel insights on the complementarities of various methods, which HFA domains and sub-domains can be administered via phone with high reliability and validity, and which HFA domains are likely to require in-person administration or other verification approaches. It is possible that the findings could be robust enough to generate correction factors for phone-based surveys that can be applied to approximate in-person measures in contexts where traditional data collection approaches are not possible (such as during health emergencies or conflict-impacted areas). Finally, the findings on response rates will be published to inform future implementation guidance on the feasibility of different methods of data collection given HFA operational constraints and measurement needs in different contexts and when each method is likely to be particularly useful.

### Conclusion

HFAs provide critical information on the quality of health service delivery, making them a vital source of data to inform the design, implementation, and evaluation of health care policies and programs. Validation studies are critical to informing how and when different types of data collection approaches are appropriate and what can be feasibly measured. This research will improve understanding on the validity of phone-based data collection approaches for HFAs to collect data on a select subset of key service delivery indicators, providing practical insights on the appropriateness, feasibility, and complementarity of different survey modalities in capturing health facility service availability and readiness. This is an important step towards building and sustaining continuous data collection, analysis, and data use for decision making across all levels of the health system in order to improve the quality of service provision, in Tajikistan and globally.
